### Intervention: Education about healthy lifestyle

The intervention will comprise education about healthy lifestyle that includes the concept of metabolic syndrome, risk factors and its prevention, the importance of lifestyle modification such as healthy diet, physical exercise, avoidance of harmful alcohol consumption, smoking cessation and stress management, as well as motivation for changing behavior. The education intervention will be delivered by experts on health education and promotion after the education package is assessed and validated by a nutritionist, physical therapist and psychologist. The education will be delivered in a one-on-one basis at their office or at any other suitable places. Every two weeks, the researcher will send a text message to the participants as a reminder asking whether they have followed the suggested healthy diet, physical activity, and mechanisms of stress management, avoidance of harmful alcohol consumption and smoking. It will also enquire as to whether they recorded their actions using the provided self-report template **(S2 File).** Throughout the intervention, the participants will be encouraged to respond to the messages, ask questions, and seek guidance. Reading materials (Handout) will also be given to each participant with the key messages of “avoid the three whites including: fat, sugar and salt, have a healthy diet, aerobic exercise, avoid sources of trans fats, avoid smoking, avoid unsafe intake of alcohol (≥ 2 drinks per day), manage your stress and avoid sitting for long time”. Additionally, a review meeting with participants will be held at the 3^rd^ and 6^th^ month of the intervention to review the key points of the intervention and reinforce, enhancing health literacy, skills, and motivation among the participants, foster encouragement and support to enhance participants’ commitment and adherence to the intervention, and reassess and identify any obstacles encountered during the intervention, and collaboratively develop strategies to overcome these barriers to change. The primary investigator will supervise the education process. Adherence to the intervention will be improved and monitored by self-report checklists, attendance at review meetings, and text message answers.

### Development of interventions

#### Dietary intervention

The World Health Organization’s recommendation for adults will help as the basis for the development of the nutritional intervention. According to the recommendation, fruit, vegetable, legumes like lentils and beans, nuts, and whole grains, such as unprocessed maize, millet, oats, wheat, and brown rice, a daily intake of at least 400g, or five portions of fruit and vegetables, excluding starchy roots like potatoes, sweet potatoes, and cassava are all parts of a healthy diet.

#### Physical intervention

The physical intervention will be designed based on the World Health Organization’s recommendation for adults aged 18–64 years. WHO recommend adults aged 18–64 years should do at least 150–300 minutes of moderate-intensity aerobic physical activity; or at least 75–150 minutes of vigorous-intensity aerobic physical activity; or an equivalent combination of moderate-and vigorous-intensity activity throughout the week.

#### Psychological intervention

Psychological intervention which includes how they manage stress, avoid the use of harmful alcohol consumption and quit smoking will be prepared based on the theory of planned behavior. Each intervention component will be assessed and validate by the experts of the field.

### Control group: General health advice

The comparator is general health advices that will be given in an individual form by the nursing professional on physical exercising, healthy diet, self-care and monitoring, according to the national guidelines recommended for non-pharmacological managements for each component of the metabolic syndrome. Education package and reading material (handout) will also be provided for them at the end of the study.

### Outcome measures

We will collect outcome measures in three waves: (at the base line, at 6^th^ and 9^th^ month of the intervention). The data collectors will be the trained BSc nurses and laboratory technologist.

#### At the baseline

Socio-demographic data, metabolic syndrome parameters and knowledge, attitude and practice (KAP) will be collected from both groups.

#### At 6^th^ month

Feasibility and acceptability of the intervention will be measured from interventional group only.

#### At 9^th^ month

Metabolic syndrome parameters and KAP will be measured from both groups.

### Independent variables

Age, sex, marital status, educational status, work experience, working hours per day, monthly income, religion, and health condition will be the independent variables of the study and will be measured by the questionnaire at the baseline.

### Dependent variables

#### Primary outcomes

*Body size (Central obesity)*. These will be defined as waist circumference > 102 cm in men, > 88 cm in women [2], and will be measured with a tape measure at the approximate midpoint between the lower margin of the last palpable rib and the top of the iliac crest or at the abdomen’s maximum extension. It will be measured at the baseline and 9^th^ month of the intervention.

*Blood pressure (BP)*. Which is defined as BP ≥ 130/85 mmHg [2, 28], and will be measured as follows: Three blood pressure measurements will be taken using appropriate size sphygmomanometer after the person is taking a rest for 5 minutes for the first measurement and with a difference of 5 minutes between successive measurements. The mean systolic and diastolic BP measurements will be considered for interpretation. The measurement will be taken at the baseline and the 9^th^ month of the intervention.

*Biochemical markers*. Fasting blood glucose (FG), high density lipoprotein (HDL), and triglycerides (TGL)) which are defined as fasting glucose ≥110 mg/dl, HDL-cholesterol < 40 mg/dl in men and < 50 mg/dl in women and Triglycerides ≥150 mg/dl respectively [2]. From each eligible individual 5 ml of venous blood will be collected at baseline and at the end of the intervention before breakfast by employing infection prevention procedures. Plasma and serum will be separated by laboratory technologist and stored at -80°C for later analyses at Bahir Dar University teaching hospital laboratory department. The tests will analyze FG, total cholesterol, HDL-C and TGL, while low-density lipoprotein will be determined indirectly.

#### Secondary outcomes

Knowledge, attitudes and practice of the participants, feasibility, acceptability, cost benefit and implementation process will be the secondary outcomes of the study.

Knowledge and attitudes towards lifestyle and cardiovascular risk factors will be assessed using a valid 43-item questionnaire which was developed and tested in India [12], and its Cronbach’s alpha for the “knowledge,” and “attitude,” are 0.72, 0.8, respectively. This questionnaire has been validated and utilized for evaluating knowledge and attitudes regarding lifestyle and cardiovascular risk factors in several studies in Ethiopia, where it was employed separately for assessing hypertension, diabetes mellitus, and lifestyle [29–32]. To simplify the citation process, we have opted to reference the tool that was developed and tested in India, as it encompasses a comprehensive questionnaire and is easily citable.

*Knowledge*. Will be assessed with 20 questions. The answers will either be recorded as a correct answer (1), an incorrect answer, or I don’t know (0). The maximum possible score is 20, and the knowledge levels will break down into Poor knowledge score (1–7), Average knowledge score (8–14), and good knowledge score (15–20) [12].

*Attitudes*. Will be assessed using 13 questions. The answers will be recorded on a 0–2 Likert scale as disagree (0), agree (1), and strongly agree (2). The highest score is 26, and the categories for attitude will: Poor attitude (scores of 0–9), Average attitude (scores of 10–18), and good attitude (scores of 19–26) [12].

*Dietary habit*, *alcohol consumption*, *smoking and physical exercise practice*. Will be evaluated using short form food frequency questionnaire. The cut-offs for fruit and vegetable servings will be as follows; Fruit: < = 2 servings/wk = 1, >2 servings /wk and < 2 servings/day = 2, > = 2 servings/day = 3, Vegetables: < = 1 servings/day = 1, 1–3 servings/day = 2, > = 3 servings/day = 3 [33].

*Stress*. Will be measured by using perceived stress scale. It is developed in 1983 and it has 10 items with total score of 40 [34].

Scores ranging from 0–13 would be considered low stress.Scores ranging from 14–26 would be considered intermediate stress.Scores ranging from 27–40 would be considered high stress.

**Feasibility** is the extent to which a new treatment, or an innovation, can be successfully used or carried out within a given agency or setting [35]. For feasibility, the criterion is practical. An intervention can be judged feasible if a task or an action can be performed relatively easily or conveniently given existing resources and circumstances like effort, time, and money, timing or sociopolitical will. It will be measured by Feasibility of Intervention Measure (FIM) [30]. These are 4-item tool for each outcome variables on a 5-point Likert scale, ranges from “Completely Disagree-Completely Agree” and score is calculated mean.

**Acceptability** is the perception among implementation stakeholders that a given treatment, service, practice, or innovation is agreeable, palatable, or satisfactory [35].

For acceptability, the criterion is personal. Two individuals can have different judgments regarding the acceptability of the same intervention based on their distinct needs, preferences, or expectations. It will be measured by Acceptability of Intervention Measure (AIM) [36]. These are 4-item tool for each outcome variables on a 5-point Likert scale, ranges from “Completely Disagree-Completely Agree” and score is calculated mean. Additionally, Sekhon’s theoretical framework for acceptability, which takes into account affective attitude, burden, ethicality, intervention coherence, opportunity costs, perceived effectiveness, and self-efficacy, will be used to evaluate acceptability from the perspectives of both deliverers and recipients.

### Cost benefit evaluation

The cost benefit evaluation will be assessed by collecting the cost data for the intervention implementation activities, which will be split into two categories: start-up costs (i.e., for screening, material preparation for education) and implementation costs (i.e., conducting educational sessions, monitoring). The cost benefit analysis will be made and the benefit would be outcome variables of the RCT and at the end we will compare them to how much costs are required for per unit of benefit. The cost benefit evaluation can be conducted separately for each outcome indicator of interest.

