**Methods and analysis:**

This randomized controlled trial will be implemented with 226 bank employees (age ≥18 years) with metabolic syndrome from government and private banks in Bahir Dar City, Ethiopia. Participants will be randomized to intervention (education) and control (general health advice) groups. The intervention group will be given one-on -one base education about healthy diets, physical exercise, stress management, avoidance of harmful alcohol consumption and smoking cessation by experts on health promotion. Text messages will be sent every two weeks and reading materials will also be provided. Additionally, a review meeting will be held at the 3^rd^ and 6^th^ month of the intervention. The primary outcomes of interest will be change in metabolic parameters (obesity levels, blood pressure, fasting blood glucose, total cholesterol, high density lipoprotein, low density lipoprotein, and triglycerides). Secondary outcomes will be knowledge, attitudes and practice of the participants towards lifestyle and cardiovascular risk factors, feasibility, acceptability, implementation fidelity, and cost-effectiveness of the intervention. Data will be collected at three time points: at baseline, at the 6^th^ month of the intervention and at the end of the intervention (9 months). Generalized linear mixed models will be utilized to compare the desired outcome between the trial arms, after accounting for baseline variations. Cost-benefit analysis and a qualitative process evaluation of the intervention will also be conducted.

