## Objectives

➢ To develop and test the effectiveness of a lifestyle education intervention on metabolic syndrome management among bank employees in Ethiopia.➢ To assess and compare the levels of knowledge, attitudes, and practices towards lifestyle and cardiovascular risk factors before and after the intervention as well as between the control and intervention groups among bank employees with metabolic syndrome in Ethiopia.➢ To assess the feasibility, and acceptability of an education intervention for healthy lifestyle on metabolic syndrome management among bank employees in Ethiopia.➢ To evaluate the cost-benefit of the educational intervention promoting healthy lifestyle to reduce risk factors for metabolic syndrome among bank employees in Ethiopia.➢ To evaluate the process of education intervention promoting healthy lifestyle to reduce risk factors for metabolic syndrome for bank employees in Ethiopia.

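### The economic analysis described is a cost-effectiveness ratio under a cost-benefit label and, because it names intervention costs only, it is not incremental over the nurse-advice control

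*Protocol article*

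**What the plan says.** The Objectives section of the protocol article includes "To evaluate the cost-benefit of the educational intervention promoting healthy lifestyle". The Cost benefit evaluation section then sets out the method in three parts.

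- **Costs.** They are obtained by "collecting the cost data for the intervention implementation activities" and fall into two groups: "start-up costs (i.e., for screening, material preparation for education") and "implementation costs (i.e., conducting educational sessions, monitoring").
- **Benefit.** The section says that "the benefit would be outcome variables of the RCT".
- **Summary.** At the end, "we will compare them to how much costs are required for per unit of benefit", and this may be done separately for each outcome.

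Elsewhere the same component goes by another name. The Abstract's list of secondary outcomes has "feasibility, acceptability, implementation fidelity, and cost-effectiveness of the intervention".

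The comparator is an active contact. Under Control group: General health advice, the advice is "given in an individual form by the nursing professional".

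**The concern.** There are two separate difficulties.

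The first is the label. A cost-benefit analysis values benefits in money, so that they can be set against costs and a net benefit stated. A cost per mmHg of blood pressure or per knowledge point leaves the benefit in natural units, which is a cost-effectiveness ratio. The described method therefore cannot answer the objective as it is worded.

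The second is the numerator. The trial compares education with nurse advice, so the economic question that matches its effect estimate is what the additional effect costs beyond nurse advice. A ratio that counts the full cost of education but none of the cost of the advice does not answer that question. Its numerator is a gross cost, while the effect it would be divided by is a contrast with the control arm.

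At stake is what can be concluded on a stated objective. Control-arm resource use is also easiest to record as it occurs, so the choice matters before the follow-up ends.

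**Working it through.** The article gives no cost, cost ratio or other economic figure, so there is no result of its own to reproduce. The check is a comparison of sections, followed by a short piece of algebra.

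**Step 1: the label, section by section.**

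| Section | Term used |
|---|---|
| Abstract, secondary outcomes | cost-effectiveness |
| Abstract, analysis sentence | cost-benefit |
| Objectives | cost-benefit |
| Study design | cost-effectiveness |
| Secondary outcomes | cost-benefit |
| Cost benefit evaluation | cost-benefit |
| Discussion | cost-effectiveness |

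The Abstract alone uses both terms. The only section that describes a method keeps the benefit in the units of the trial outcomes and mentions no monetary valuation. That method matches the cost-effectiveness label and not the objective.

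**Step 2: the numerator.** Four items are named: screening, preparation of materials, educational sessions and monitoring. They are presented as intervention costs, and both lists are introduced by i.e., which reads as a definition and not as examples. No control-arm item appears, and no difference in cost between arms is described. The control arm nevertheless uses nurse time for each participant, so its cost is above zero.

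**Step 3: the denominator.** The Cost benefit evaluation section does not say how the benefit is contrasted. The Statistical analysis section judges effectiveness on the metabolic indicators by comparing the groups' changes between baseline and month 9. Read together, the benefit for those indicators is the between-arm difference, and that is used here.

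**Step 4: size of the discrepancy.** Let C1 and C0 be the mean cost per person in the intervention and control arms, c = C0/C1, and D the between-arm difference in change.

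- Ratio as written: C1 / D
- Incremental ratio: (C1 - C0) / D = C1(1 - c) / D
- Ratio as written divided by incremental ratio: 1 / (1 - c)
- Overstatement: 1/(1 - c) - 1

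D cancels, so the result does not depend on the outcome chosen or on the effect size. The values of c are assumptions:

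- c = 0: 1/1.00 = 1.00, no overstatement
- c = 0.10: 1/0.90 = 1.11, overstatement 11%
- c = 0.25: 1/0.75 = 1.33, overstatement 33%

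As an illustration, take C1 = 100 arbitrary units and D = 6.4 mmHg, the systolic difference used in the Sample size section. The ratio as written is 100/6.4 = 15.6 units per mmHg. The incremental ratio is 90/6.4 = 14.1 at c = 0.10 and 75/6.4 = 11.7 at c = 0.25.

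**The case against.** The best counter-argument is that this is a short paragraph in a journal article. Perspective, comparator costing and uncertainty are commonly left to a fuller plan, and the text does not say that control costs are excluded. That is fair as far as silence goes, and it would be wrong to assert that the control costs will never be collected. But the section is not merely silent: it states which costs are collected, ties them to intervention activities and lists them. A fuller plan would also leave the published objective and the published method in conflict over the label.

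Four stronger readings are tempting, and the document does not support them.

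- **That the cost per unit will be wrong.** No cost is given. If nurse advice is cheap relative to one-on-one education, fortnightly texts, handouts and two review meetings, the ratio is close to the incremental one. A control share as high as 50%, which would double the ratio (1/0.50 = 2.00), fits poorly with the two arms as described.
- **That a within-arm change will be the benefit**, which would pull the ratio down. The Statistical analysis section points to the between-group difference for the metabolic indicators. What remains open is narrower: before-and-after comparisons are also planned for knowledge, attitudes and practice, and feasibility and acceptability are measured in the intervention arm only.
- **That the cost result is meant to drive scale-up.** The Introduction links scale-up to evidence on effectiveness, feasibility and acceptability and does not mention cost there.
- **That listing screening as a start-up cost is an error.** Screening takes place in both halves of the city, but a roll-out would also have to find eligible staff. Whether to count it is a choice of perspective, which needs only to be stated.

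**Conclusion.** The point holds in two parts. First, the method described is a cost-effectiveness ratio. The cost-benefit objective cannot be met by it, and the article is inconsistent about which analysis it promises. This part rests on the text alone.

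Second, the costs named are one-armed against an active comparator, so the ratio as written is not incremental. With the between-arm difference as the benefit, it overstates the incremental cost per unit by 1/(1 - c) - 1, which is 11% at c = 10% and 33% at c = 25%. These shares are assumptions. The direction follows from the control cost being above zero and below the intervention cost, and from the between-arm difference being the denominator. The size may be small.

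The matter affects a secondary outcome. It leaves the primary effectiveness result untouched, but it limits what the economic objective can conclude, and it is cheap to correct before the analysis.

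**What to change.** - **Label.** Call the component a cost-effectiveness analysis in every section listed above. If cost-benefit is really intended, state how benefits will be valued in money.
- **Costs.** Record nurse time and materials in the control arm on the same basis as the education arm.
- **Ratio.** Define it as the difference between arms in mean cost per person, divided by the between-arm difference in change from baseline to month 9 already set out under Statistical analysis. Limit it to outcomes measured in both arms.
- **Screening.** State whether it is counted as a programme cost. If it is counted equally in both arms, it cancels from the cost difference. If it is meant as a cost of roll-out, say so.

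The price is a time-and-materials log for the control nurse and revised wording, so slightly more record keeping. If control contacts have already taken place, nurse time would have to be reconstructed and the assumption reported.

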### Process evaluation

Concurrent process evaluation design will be implemented to evaluate the process of education intervention for promoting healthy lifestyle to reduce risk factors for metabolic syndrome, among office workers in Ethiopia.

**Fidelity** is defined as the extent to which an intervention is delivered as proposed. It will be checked based on the five main dimensions (Adherence, exposure or dose, quality of delivery, participant responsiveness and program differentiation of the interventions [35, 37]. It will be evaluated by participants and providers self-reports and researcher observations using the prepared checklist **(S3 File)**.

**Implementation process** will be evaluated using the Consolidated Framework for Implementation Research model [38]. The model contains five domains, including intervention, outer setting, inner setting, individuals involved and process. These five dimensions will be used to evaluate the study’s implementation process. Participant self-report method will be used to collect the data. Self-report format will be provided to each participant and they will be requested to list down the barriers they faced while they implement the intervention instructions **(S2 File).** If the data that are collected by self-report are not sufficient, interview will be implemented to collect further data at the end of the trial until data saturation and the interview topic guide will be informed by the Consolidated Framework for Implementation Research (CFIR) [32]. Then barriers will be identified for future successful large-scale randomized control trials.

### Data collection and safety monitoring

The trial data safety and adverse effect monitoring committee (DSMC) will be established to monitor the adverse effects of the intervention on participants. Experts in health promotion, laboratory technologists, nurses, and officials will make up the committee. Because the intervention won’t directly involve any invasive procedures or administer drugs that could affect study participants, there won’t be any potential for adverse risks or harms. The DSMC will be used as the protocol for data reporting that minimize bias. The principal investigator will keep track of all adverse events and connect them to the appropriate local health organization if any.

Data will be collected by trained BSc nurses and Laboratory technologist. Waist circumference, blood pressure, and blood sample will be taken at the workplace or another location the participant chooses. Data on knowledge, attitude, and practice about a healthy lifestyle and cardiovascular risk factors will be collected at their office. As well data on the feasibility and acceptability of the intervention will be collected at their office during the review meeting that will be held at the 6^th^ month of the intervention.

The data will only be accessible to the research team, and identifiable information will be kept apart from the rest of the data. Unless the participants have chosen differently, results will only be reported in collective and will not identify them specifically. Data will be securely stored on password-protected computers in the National Centre for Epidemiology and Population Health at the Australian National University. Hard copies of records will be kept in a locked filing cabinet in my office. All research data will be kept for at least five years after publications resulting from the study and securely stored. Following the storage term, all personally identifying information will be eliminated from the data, which will then be archived at the Australian Data Archive (www.ada.edu.au) for use in future research, may be by other researchers as well.

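### Feasibility and acceptability scales are collected only at the 6-month review meeting, an intervention session whose attendance is an adherence marker, so their means risk being too favourable

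*Protocol article*

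**What the plan says.** Under the month-6 heading of Outcome measures, the protocol article says: "Feasibility and acceptability of the intervention will be measured from interventional group only". The section Data collection and safety monitoring fixes the occasion: "feasibility and acceptability of the intervention will be collected at their office during the review meeting", and it names the month-6 meeting as the one meant. The month-9 heading lists only metabolic parameters and KAP, so no later collection of the two scales is stated.

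The section Intervention: Education about healthy lifestyle places the review meetings (months 3 and 6) inside the intervention. Among their aims is to "foster encouragement and support to enhance participants’ commitment and adherence to the intervention". The same section says that adherence is to be improved and "monitored by self-report checklists, attendance at review meetings, and text message answers".

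Under Secondary outcomes, feasibility and acceptability are each scored with a four-item tool on a 5-point agreement scale and summarised as a mean. A theoretical framework "will be used to evaluate acceptability from the perspectives of both deliverers and recipients" as well. Feasibility and acceptability also appear as an objective of their own under Objectives.

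**The concern.** Being scored on acceptability depends on turning up to a session of the programme being rated, and the protocol itself treats turning up as a sign of adherence. People who find the programme burdensome or impractical are plausibly the least likely to attend, and the article names no other way of obtaining their scores. If so, the mean describes attenders, not everyone offered the intervention, and the likely error is in the favourable direction.

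These are single-arm means, so there is no control group in which such a selection effect could cancel. The Introduction says the evidence is meant to help policy makers scale up the strategy, a use for which the views of the less engaged matter most.

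The article does not tie its other measurements to a session. Waist, blood pressure and blood are taken at work or elsewhere at the participant's choice, and KAP is collected at the office. Only these two scales depend on attending a meeting.

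**Working it through.** **Inputs from the article**
- Intervention group size: 113 (Sample size). This follows from 94 x 1.2 = 112.8, rounded up.
- Planned attrition: 20% (Sample size).
- Scales: four items each, 5-point, reported as a mean (Secondary outcomes).
- Expected attendance at the review meeting: not given.
- Expected scores, or any difference between attenders and non-attenders: not given.

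The article therefore has no figure of its own on this point to reproduce, and the size can only be shown over an assumed range.

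**Formula.** Let a be the share of the intervention group attending, and D the attender mean minus the mean that non-attenders would have given. The mean over everyone is a x (attender mean) + (1 - a) x (non-attender mean). Subtracting this from the attender mean gives

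overstatement = (1 - a) x D.

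**Results (a and D both assumed)**

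| Attendance a | Respondents of 113 | D = 0.5 | D = 1.0 |
|---|---|---|---|
| 100% | 113 | 0 | 0 |
| 90% | about 102 | 0.1 x 0.5 = 0.05 | 0.1 x 1.0 = 0.10 |
| 80% | about 90 | 0.2 x 0.5 = 0.10 | 0.2 x 1.0 = 0.20 |
| 70% | about 79 | 0.3 x 0.5 = 0.15 | 0.3 x 1.0 = 0.30 |
| 60% | about 68 | 0.4 x 0.5 = 0.20 | 0.4 x 1.0 = 0.40 |

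Over 60-90% attendance the range is 0.05 to 0.40 points. If D is zero there is no bias at any attendance.

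**How much of this comes from the collection rule.** Some non-attenders will have left the trial and could not be scored by any method. Split the non-attenders into dropouts (share d) and reachable people who missed the meeting (share m), so that a = 1 - d - m, and assume the same D for both. Scoring the reachable people lowers the reported mean by m x D / (1 - d).
- a = 80%, d = 20%, m = 0: reduction 0. The whole 0.20 (at D = 1.0) remains.
- a = 70%, d = 20%, m = 10%: reduction 0.10 x 1.0 / 0.80 = 0.125. Of 0.30, 0.175 remains.
- a = 60%, d = 20%, m = 20%: reduction 0.20 x 1.0 / 0.80 = 0.25. Of 0.40, 0.15 remains.

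The 20% is borrowed from the sample-size section as an illustration; it is not a forecast of loss by month 6.

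**The case against.** The strongest reply is that no bias has been shown. Attendance and the gap are both unknown, and at full attendance the problem disappears. Several features may keep attendance high: the data are collected at participants' offices, people not available throughout the programme are excluded, and the workforce is described as stable and willing. Attendance is one of three adherence markers, so an attender is not necessarily adherent and may still give low ratings. All of this stands, and it makes the point a conditional risk.

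The meeting is also meant to bring out obstacles, and data collection is assigned to nurses and a laboratory technologist while health promotion experts deliver the education. The worry that answers are coloured by being given inside the session is therefore weak, and I put no number on it.

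There is other evidence on acceptability and barriers: deliverers' views, each participant's self-report barrier form, and end-of-trial interviews if those forms are insufficient. These inform the wider conclusions, but none is stated to supply scale scores for people who miss the meeting. The Statistical analysis section concedes in general that people without follow-up data cannot be assessed, and it promises a CONSORT flow diagram. Neither gives a denominator for the two scales or separates attenders from non-attenders.

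Finally, this is a condensed article, and the full protocol may provide for make-up contact. That is possible, and the article does not say that non-attenders will be left out. But the collection occasion is a rule the article chose to state, and the point concerns that rule.

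**Conclusion.** The point holds as a risk. Followed as written, the stated rule selects respondents on attendance at an intervention session, and the mean feasibility and acceptability scores would be too high if attendance is incomplete and non-attenders would rate lower. The size is 0.05 to 0.40 points on a 5-point scale under assumed attendance of 60-90% and an assumed gap of 0.5-1.0 point. It is zero at full attendance, and only the part due to reachable non-attenders can be removed.

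A reader might infer that the scores will come mainly from adherent participants and will overstate acceptability. The document does not support that: it gives no attendance figure and no gap, and attendance alone does not define adherence.

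The consequence is limited. These are secondary, descriptive outcomes in one group, the article states no acceptability threshold that a shift could cross, and the between-group comparison of metabolic and KAP outcomes is unaffected. It is worth correcting because it bears on a stated objective and the correction is cheap.

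**What to change.** - Separate the scales from the meeting. Have the data collectors offer both four-item scales to every intervention participant in a window around month 6, by office visit or phone, whether or not the person attends.
- Use the month-9 visit, which is already planned, for anyone still missing, and flag those answers as late.
- Record attendance at the month-6 meeting. Report respondents out of all allocated to the intervention, and give the means for attenders and non-attenders separately as well as overall.

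The cost is an eight-item form for the non-attenders and a few extra contacts. The drawback is that some ratings are given after month 6 and so refer to a longer exposure, which is why they should be flagged and the month-6 means also shown alone. If month-6 collection is already complete, the reporting step can still be done and would keep attenders' scores from being read as those of the whole group.
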